## Abstract

**Background:**

Patients with ulcerative colitis (UC) often face complex treatment decisions. Although shared decision making (SDM) is considered important, tools to facilitate this are currently lacking for UC. A recent pilot study of a novel Web-based decision aid (DA), my Actively Informed Decision (myAID), has suggested its acceptability and feasibility for informing treatment decisions and facilitating SDM in clinical practice.

**Objective:**

This paper describes the study protocol of the myAID study to assess the clinical impact of systematic implementation of myAID in routine UC management.

**Methods:**

The myAID study is a multicenter, cluster randomized controlled trial (CRCT) involving 22 Australian sites that will assess the clinical efficacy of routine use of myAID (intervention) against usual care without access to myAID (control) for UC patients. Participating sites (clusters) will be randomly allocated in a 1:1 ratio between the 2 arms. Patients making a new treatment decision beyond 5-aminosalicylate agents will be eligible to participate. Patients allocated to the intervention arm will view myAID at the time of recruitment and have free access to it throughout the study period. The effect of the myAID intervention will be assessed using the results of serial Web-based questionnaires and fecal calprotectin at baseline, 2 months, 6 months, and 12 months. A Web-based questionnaire within 2-4 weeks of referral will determine early change in quality of decision making and anxiety (both arms) and intervention acceptability (intervention arm only).

**Results:**

Study recruitment and funding began in October 2016, and recruitment will continue through 2020, for a minimum of 300 study participants at baseline at the current projection. The primary outcome will be health-related quality of life (Assessment of Quality of Life-8D), and secondary outcomes will include patient empowerment, quality of decision making, anxiety, work productivity and activity impairment, and disease activity. In addition, we aim to determine the predictors of UC treatment decisions and outcomes and the cost-effectiveness of implementing myAID in routine practice. Feedback obtained about myAID will be used to determine areas for improvement and barriers to its implementation. Completion of data collection and publication of study results are anticipated in 2021.

**Conclusions:**

myAID is a novel Web-based DA designed to facilitate SDM in UC management. The results of this CRCT will contribute new evidence to the literature in comparing outcomes between patients who routinely access such decision support intervention versus those who do not, across multiple large inflammatory bowel disease centers as well as community-based private practices in Australia.

**Trial Registration:**

Australian New Zealand Clinical Trial Registry ACTRN12617001246370 http://anzctr.org.au/Trial/ Registration/TrialReview.aspx?ACTRN=12617001246370

**International Registered Report Identifier (IRRID):**

DERR1-10.2196/15994

## Introduction

### Background

Ulcerative colitis (UC) is a chronic disabling inflammatory bowel disease (IBD). It affects about 40,000 people in Australia [1], with its incidence and burden rising globally [2]. Although half of these patients may be managed with 5-aminosalicylates (5-ASAs) alone [3], the rest will face decisions about other treatments that require long-term immunosuppression and even colectomy. These decisions are complex because they involve not only the identification of the best treatment strategy to prevent symptoms and progression of the disease but also consideration of the trade-offs of the available treatment options that differ in their efficacy and potential risks, modes of delivery, and dosing intervals. Therefore, patients’ values and preferences heavily influence treatment choice and adherence, and a more collaborative and empowering approach to help navigate the complex benefit-risk profiles of these treatment options is important in guiding the decision-making process [4,5].

A recent survey confirmed that such a process of patient engagement or shared decision making (SDM) is desired by patients with UC [6]. SDM helps the doctor and the patient to collaborate on management decisions, which can lead to improved quality of life (QoL) and likelihood of achieving health goals, while lowering the demand for health care resources and improving patients’ health care experience [7]. Many health care organizations have embraced SDM as an important part of health care standards and patient-centered care [8-10].

Decision aids (DAs) are tools developed to facilitate SDM by presenting patients with evidence-based information in a patient-friendly format and encouraging active engagement in the decision-making process. A recent Cochrane review indicates that their use in other chronic diseases can improve patient knowledge and reduce decisional conflict and the number of patients remaining undecided or being passive in the decision-making process [11]. With increasing acceptance and familiarity of online tools, Web-based DAs are gaining popularity [6,12,13].

Although using DAs use has the potential to facilitate SDM and participatory medicine in UC management, their uptake and application in clinical practice to date have been limited. Available electronic health technologies have suffered from high attrition rates [14], and patient and clinician perspectives on the best approach to the use of these tools in routine clinical practice remain poorly understood. A participatory health research design to increase involvement of patients and clinicians in their development and subsequent implementation has been suggested as a potential way of increasing their effectiveness and overcoming these limitations.

Recently, a new Web-based DA was developed for use in UC, which, for the first time, includes an interactive video discussing both medical and surgical treatment options in UC management, with the aim of facilitating SDM. Patients and a multidisciplinary panel of clinical experts were involved in its design, with a rigorous evaluation process [15] and close reference to the International Patient Decision Aids Standards checklist [16]. Originally developed in the United States, the DA was modified for use by an Australian audience in this study and named myAID (for my Actively Informed Decision; Emmi Solutions). A pilot study confirmed the acceptability of myAID to both patients and clinicians as a feasible SDM tool for UC management ([name] et al, unpublished data, 2020). To investigate whether routine use of myAID to promote SDM will translate to improvement of meaningful outcomes for patients, we designed a national cluster randomized controlled trial (CRCT) to test its efficacy against usual care. The CRCT is hereafter referred to as *the myAID study*.

### Research Objectives

The overall aim of this study is to assess the impact of systematic use of myAID by eligible patients with UC on patient-reported UC clinical outcomes over a period of up to 12 months. Specific objectives of this study are as follows:

Comparison of changes in health-related QoL (primary outcome) from baseline to 6-month follow-up in patients accessing myAID (intervention arm) versus patients receiving usual care.Comparison of differences in patient empowerment, quality of decision making, anxiety, work productivity, and disease activity including steroid use, hospital visits, and colectomy (secondary outcomes) in patients accessing myAID versus patients receiving usual care at the 6-month follow-up.Determine the predictors of health literacy in patients with UC and the relationship between health literacy, decisional conflict, and treatment choices.Determine the cost-effectiveness of implementing myAID in routine practice.Investigate the views of study participants about myAID and determine areas for improvement or barriers to implementation in clinical practice.

## Methods

### Trial Design

The myAID study is a multicenter CRCT (see Figure 1) using a parallel arm design. Sites will be randomly allocated in a 1:1 ratio between intervention (routine use of myAID) and control (usual care without access to myAID) arms, with each site constituting a single cluster. Patients managed privately by the clinicians practicing at that site will also be grouped into the same cluster. As the intervention requires viewing and interacting with myAID, this is an open-label study with participants and their treating clinician and team being aware of their group allocation. Although only the patients, their family, and clinicians allocated to the intervention arm will be able to access and view myAID during the course of the study, participants from both groups may access other resources either sought independently or as recommended by their treating team, such as printed or online resources via patient organization websites. The use of such resources will be documented via participant questionnaires.

**Figure 1 figure1:**
[figure not shown]
myAID study flowchart. 5-ASA: 5-aminosalicylates; UC: ulcerative colitis; myAID: my Actively Informed Decision. *Decision consult, if arranged, will be arranged within 2-4 weeks of referral. **Post decision consult (if arranged) or follow-up questionnaire to be completed within 2-4 weeks of referral.

### Setting

This study will be undertaken at 22 sites in 5 of the 6 states in Australia, including large public IBD clinics and community-based private practices in urban and regional areas. Patient enrollment commenced in October 2016, with 21 of the 22 sites currently enrolling participants. All data collection (all participants) and viewing of myAID (intervention participants) will be undertaken off-site.

### Study Population and Eligibility

#### Trial Inclusion Criteria

Patients presenting to the outpatient clinic at the participating sites will be eligible if they (1) have a diagnosis of UC, (2) are 18 years or older, (3) need to make a new decision about their UC management following a lack of response to (previous or current) 5-ASA treatment, and (4) can consent and read the myAID information online in English.

New decisions about management will have to specifically involve discussions around dose escalation, addition or change in treatment. This may include 5-ASA dose increase or addition of either oral and topical treatment, addition or dose increase of steroids, thiopurines, methotrexate, tofacitinib, and biologic agents as well as discussion regarding better treatment adherence. Consented patients could continue as study participants if they underwent colectomy after study enrollment, provided that this decision was made after baseline assessment and viewing of myAID (for the intervention group).

#### Trial Exclusion Criteria

The exclusion criteria will be as follows:

New diagnosis of UC (diagnosis within 4 weeks before referral) or no prior experience with 5-ASALack of need for treatment escalation, addition or change in treatment (including patients who have already undergone colectomy at the time of referral),Current episode of acute severe colitis requiring inpatient treatmentNot having access to a computer with internet outside of the clinic.

#### Intervention—my Actively Informed Decision

The development, key features, and feasibility testing of the myAID intervention were previously described in a pilot study ([name] et al, unpublished data, 2020). In brief, myAID (Emmi Solutions) is a Web-based multimedia DA incorporating an interactive video (Figure 2), which has been designed to help prepare viewers for decision making about their UC treatment. Its content has been structured to deliver information aimed at improving the viewer’s understanding of UC as well as the available medical and surgical treatments, including their potential benefits and risks, and to elicit the viewer’s treatment goals and preferences through a series of interactive questions. The current version is accessible using a computer with an internet connection but is not downloadable or accessible on a mobile device. It takes approximately 32 min to view uninterrupted, with the actual time varying with content watched and time taken with interactive elements.

Patients (and their invited family members) allocated to the intervention arm will have free access to myAID during the period of the study through their designated URL, which will be provided to them upon completion of their baseline Web-based questionnaire. They will be able to view myAID at any location using a computer, provided there is internet access. All patients will confirm their first complete viewing of myAID via their Web-based questionnaire. Patients will report any technical issues with regard to access or use of myAID via email for assistance by the research team. myAID access by these study participants will also be tracked by Emmi Solutions and reported back to the myAID study group on a monthly basis. The treating clinicians allocated to the intervention arm will similarly have free access to myAID during the study period.

**Figure 2 figure2:**
[figure not shown]
Screenshots of myAID (myAID@2015 Emmi Solutions, LLC). myAID: my Actively Informed Decision.

#### Recruitment and Informed Consent

Patients who are eligible for the study will be identified by their respective consultant gastroenterologist who will obtain verbal consent (or written consent, if specifically required by their local ethics governance) for the interested patient’s contact details to be forwarded onto the myAID study group. Referred patients will then receive a study invitation email with an attached electronic participant information booklet, followed by a phone call from the study research assistant to confirm receipt of the study information and provide a verbal explanation of the study. A chance to win an Aus $200 (US $123) gift voucher will be used as an incentive for participation and completion of questionnaires. Those who wish to proceed will then be sent a further email with their unique study ID and a URL, which they will use to provide online consent and complete the baseline questionnaire and a laboratory request form for fecal calprotectin (FC) testing within 3 weeks from the time of the referral to the study. Patients who did not comply with the required timeframe can be re-referred provided they still meet the study inclusion criteria.

#### Study Flow and Data Collection

All patients completing their baseline Web-based questionnaire will be entered into the study database and continue to be followed up by the myAID study group for 12 months unless they withdraw their consent. All participating sites will continue to provide usual care, although we will ask that a brief follow-up, either in the form of a face-to-face or telephone consultation (referred to as a *decision consult*), be arranged at 2-4 weeks after patient referral to the study if possible. Although not mandated for the study, this was felt to be important by clinicians in our pilot study to facilitate SDM.

Web-based questionnaires (using the SurveyMonkey platform) are administered to study participants at baseline, 2-4 weeks (or following the *decision consult* if arranged), 2 months, 6 months (primary and secondary outcome assessment), and 12 months (long-term impact). Table 1 summarizes the outcome measures captured at each timepoint. Study participants will be sent a URL for the questionnaires via email at each of these time points, as this was deemed acceptable and feasible from the pilot study ([name] et al, unpublished data, 2020).

All participants will be asked to submit their stool samples at baseline, 2 months, 6 months, and 12 months. Each site will provide the study participant with a preassembled stool sampling kit at the time of referral. Study participants will be asked to submit their samples to their local Sonic Healthcare pathology laboratory (nationwide pathology provider owned by Sonic Healthcare Limited), where the FC will be measured using a quantitative fluoroenzyoimmunoassay (EliA Calprotectin 2; Thermo Fisher). Participants residing outside of Adelaide in South Australia will use the SA Pathology laboratory (statewide pathology provider for the public health sector in South Australia) that uses the same assay for FC testing. Participants who do not have access to either of these labs will be asked to submit their samples to an alternative local pathology lab. All FC measurements will be performed according to the manufacturer’s instructions without knowledge of patient data. Concentrations will be expressed as micrograms per gram of stool.

We will accept patient referrals until 2020 to reach our target recruitment sample and follow-up participants for up to 12 months, thereby completing data collection in 2021.

**Table 1 table1:** myAID study outcome measures.

Outcome measures	Baseline (within 3 weeks of referral)	Within 4 weeks	2 months	6 months	12 months
Assessment of Quality of Life-8D	✓^a^	N/A^b^	✓	✓	✓
Health Education Impact Questionnaire	✓	N/A	✓	✓	✓
Health Literacy Questionnaire	✓	N/A	✓	✓	✓
Decisional Conflict Scale	✓	✓	✓	✓	✓
Trust in Physician Scale	✓	✓	✓	✓	✓
Hospital Anxiety and Depression Scale-Anxiety	✓	✓	✓	✓	✓
Simple Clinical Colitis Activity Index	✓	N/A	✓	✓	✓
Fecal calprotectin	✓	N/A	✓	✓	✓
Clinical outcomes	✓	N/A	✓	✓	✓
Work productivity and activity index	✓	N/A	✓	✓	✓
myAID acceptability	N/A	✓	N/A	N/A	N/A

^a^✓: included.

^b^N/A: not applicable.

#### Measures

##### Patient Demographics, Disease, and Treatment Characteristics

Upon consenting, all patients will complete a Web-based questionnaire to provide the following:

Socioeconomic data—age, gender, ethnicity, postal code, language spoken at home, relationship, education, employment and smoking status, and health insurance coverage.Clinical data—time since diagnosis, disease extent, previous hospital visits and admissions for UC, comorbidities, UC-related surgical history, previous and current treatment history including systemic corticosteroid use, main setting for clinical care (public vs private), and access to an IBD nurse.

#### Review

##### Outcome Measures

The primary outcome for the study is *QoL* as measured by the 35-item Assessment of Quality of Life-8D (AQoL-8D) [17]. AQoL-8D is a health-related multi-attribute utility QoL instrument that measures 8 dimensions within 2 *super-dimensions*: Physical (independent living, pain, and senses) and psychosocial (mental health, happiness, coping, relationships, and self-worth). AQoL-8D has previously been used in economic evaluation studies in both Crohn disease (CD) [18] and UC [19]. Each item is scored on a 4- to 6-point Likert scale based on a recall period of 7 days, and these are reduced to a single utility score using an algorithm that also generates an index number for each of the 8 dimensions and for the 2 *super-dimensions*.

The secondary outcomes for the study are as follows:

*Empowerment*. This will be measured by the Health Education Impact Questionnaire 3.0 (heiQ) [20] using 4 of its dimensions (32 items): positive and active engagement in life, constructive attitudes and approaches, self-monitoring and insight, and emotional well-being. Items are recorded on a 4-point Likert scale from 1 to 4, where 1=strongly disagree and 4=strongly agree. The items in each dimension are summed, and the sum is divided by the number of items to generate a score for each dimension. The heiQ was developed to assess the outcomes of patient education programs, with higher scores indicating better self-management and knowledge, except for the emotional well-being scale, which is reversed.*Health literacy*. This will be measured by the 44-item Health Literacy Questionnaire (HLQ) [21]. The HLQ covers 9 domains, each consisting of 4 to 6 items measured on either 4- or 5-point Likert scales. There is no one overall summative score; the score for each domain is generated by following a computerized algorithm using SPSS or Microsoft Excel. The included domains capture how the patients engage, access, and use health information and services and provide an opportunity for reflection of the quality of health and social service provision.*Quality of decision making*. This will be measured by the 16-item Decisional Conflict Scale (DCS) [22] and the 11-item Trust in Physician Scale (TPS) [23]. DCS measures uncertainty in making a choice, modifiable factors contributing to the uncertainty, and perceived effective decision making, with a score of 1 indicating low decisional conflict and 5 indicating high decisional conflict. All items are based on a 5-point Likert scale ranging from strongly disagree to strongly agree. Total scores and subscale scores can be summed, divided by the number of items, and then converted to a 0 to 100 scale. TPS, on the other hand, measures the degree of interpersonal trust in a physician with regard to dependability, confidence, and confidentiality of information. All items are scored on a 5-point Likert scale ranging from *strongly agree* (5) to *strongly disagree* (1), and a summary measure of trust can be obtained by taking the unweighted mean of the responses (negatively worded items are reverse-scored) and transforming that value to a 0 to 100 scale.*Anxiety*. This will be measured by the 7-item Hospital Anxiety and Depression Scale-Anxiety (HADS-A) [24]. The HADS-A is a self-assessment mood scale scored on a 4-point Likert scale and reported as a sum score ranging from 0 to 21, with a higher score indicating a greater level of anxiety symptoms.*UC disease activity*. This will be measured by the patient-reported 13-item Simple Clinical Colitis Activity Index (SCCAI) [25] and FC. SCCAI is a symptom-based clinical score for UC with a score range of 0 to 19, with a higher score indicating greater disease activity. Although originally intended for clinician use, recent studies have allowed patients to complete the SCCAI themselves [26,27]. FC is an increasingly accepted biomarker for the assessment of disease activity in IBD. The upper limit of the normal range of FC in patients without gut inflammation is well defined as less than 50 µg/g [28].*Clinical outcomes*. These will be captured by 4 items included in the Web-based questionnaire asking patients to report on their use of systemic corticosteroids, need for UC-related surgery, emergency department visits, and hospital admissions. Responses to these items will be used to initiate chart reviews for validation and to calculate: (1) proportion of patients taking steroids, (2) proportion of patients requiring surgery, and (3) number and days of unplanned emergency department visits and hospital admissions.*Work productivity*. This will be measured by the 6-item Work Productivity and Activity Impairment questionnaire (WPAI) [29]. The WPAI measures 4 domains of the impact of disease on impairment in work or other activities (absenteeism, presenteeism, overall work productivity loss, and activity impairment). It is self-reported using a 1-week recall period, and domain scores are expressed as percentage of impairment, with higher scores indicating worse work-related outcomes.*Acceptability of myAID*. This will be measured by a Web-based questionnaire at 2 to 4 weeks from the time of referral (or following the *decision consult* if arranged) for the intervention group. We will seek intervention group participants’ views about the ease of viewing myAID, adequacy of its content, optimal timing for receipt of myAID, and the extent to which it facilitated understanding of their condition and the available treatment options, and ultimately, whether it aided in the discussion of treatment with their clinician. We will also determine whether additional resources were sought or prescribed and whether a *decision consult* was considered necessary in the decision-making process.

Patients who undergo colectomy during the study will complete a modified questionnaire that does not include the SCCAI and will no longer submit stool samples for FC measurement.

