### Withdrawal

Study participants will be able to withdraw from the study whenever they wish without giving a reason and without affecting their care. We will document their reasons for withdrawal if provided as well as any feedback regarding myAID. If a participant misses 1 assessment, we will encourage them to continue the study and complete the subsequent questionnaires and FC testing at the designated time points. Patients who undergo colectomy during the study period will remain in the study unless they specifically choose to withdraw. Data collection from these patients will be altered as previously described.

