##### External Imputation of Outcome Measures

If the entire questionnaire at a specific time point is missing, we will impute missing scores by appropriate regression models using all available values of that score at other time points for the individual and other participants belonging to the same allocated group. We will also consider using other predictors from patient demographics and disease activity, although they may only play a limited role in predicting missing values.

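### An arm-specific condition on staying in the study after colectomy conflicts with intention to treat, and the SCCAI and calprotectin comparisons have no stated rule for colectomy

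*Protocol article*

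**What the plan says.** **Retention.** Trial Inclusion Criteria allows consented patients who later have a colectomy to continue, "provided that this decision was made after baseline assessment and viewing of myAID (for the intervention group"). Three other places in the protocol article differ:

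- Study Flow and Data Collection has every patient who completes the baseline questionnaire followed for 12 months unless consent is withdrawn.
- Withdrawal states: "Patients who undergo colectomy during the study period will remain in the study unless they specifically choose to withdraw".
- Outcome Data Analysis makes the primary analysis intention to treat.

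According to the description of the intervention, the myAID link is issued only once the baseline questionnaire is complete.

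**Measurement after colectomy.** Outcome Measures says that these patients "will complete a modified questionnaire that does not include the SCCAI and will no longer submit stool samples for FC measurement". The other questionnaires, AQoL-8D included, continue.

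**Where colectomy is counted.** Research Objectives lists, for comparison at 6 months, "disease activity including steroid use, hospital visits, and colectomy (secondary outcomes"). Outcome Measures also derives a separate "2) proportion of patients requiring surgery", with chart review to validate patient reports.

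**Missing data.** General Principles looks at missingness measure by measure. Unless systematic problems emerge, it commits to imputing, and it does not mention colectomy. External Imputation of Outcome Measures covers a narrower case: "If the entire questionnaire at a specific time point is missing, we will impute missing scores by appropriate regression models using all available values".

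**The concern.** Two separate problems meet at colectomy.

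The first is a post-randomisation exclusion that applies to one arm. Viewing myAID happens after allocation and only in the intervention arm. A control patient who decides on surgery soon after baseline stays in. An intervention patient who decides at the same moment, but has not yet watched myAID, does not meet the stated condition. Early and possibly severe cases could therefore leave one arm only. Everything measured on them would go too, including the primary outcome and the count of operations.

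The second is that SCCAI and calprotectin are cut off by an event that is itself related to disease activity. myAID explains surgical as well as medical options, so it could plausibly change how many patients choose surgery. Analysing only those still measured then compares groups selected after randomisation. Imputing predicts a colitis score and a stool marker as though the colon were still in place. The article does not say which of these will be done.

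**Working it through.** **1. The retention texts side by side.** Take a patient who completes baseline and decides on colectomy before any viewing of myAID could take place.

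| Text | Control arm | Intervention arm |
|---|---|---|
| Trial Inclusion Criteria | stays (decision after baseline) | condition not met (myAID not viewed) |
| Study Flow and Data Collection | followed for 12 months | followed for 12 months |
| Withdrawal | remains | remains |
| Outcome Data Analysis | analysed as randomised | analysed as randomised |

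The first row differs by arm and the other three do not. Because the link arrives only after baseline, there is always some interval in which an intervention patient can fail the condition. The documents do not say how long it is or how many patients decide within it, so the bias cannot be sized. For scale, with 119 per group, each intervention patient removed after surgery takes 1/119 = 0.8 percentage points off that arm's surgery proportion.

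**2. Which imputation text applies.** A colectomy patient returns a modified questionnaire, so the questionnaire is not wholly missing and the regression method under External Imputation does not clearly apply. The general commitment is wider and has no colectomy exception. The status of these scores is therefore open.

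**3. Size of the effect on SCCAI and calprotectin if colectomy patients are dropped.** The plan states no colectomy rate and no SD for either measure, so there is no figure of its own to reproduce here. All rates below are assumed.

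Model: the same standard normal severity in both arms, no true effect, and colectomy removes exactly the sickest fraction p. The mean of those left is −φ(z)/(1−p), where z is the upper-p point.

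| p | φ(z) | mean of those left (SD) |
|---|---|---|
| 2% | 0.0484 | −0.049 |
| 4% | 0.0862 | −0.090 |
| 3% | 0.0680 | −0.070 |
| 6% | 0.1191 | −0.127 |
| 5% | 0.1031 | −0.109 |
| 10% | 0.1755 | −0.195 |

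Gaps in favour of the arm with more surgery:

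- 2% vs 4%: 0.040 SD
- 3% vs 6%: 0.057 SD
- 5% vs 10%: 0.086 SD

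**4. A milder selection model.** Let colectomy patients be d SD worse than average rather than exactly the top tail. The gap is d × [pA/(1−pA) − pB/(1−pB)]. For d from 0.5 to 2:

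- 2% vs 1%: 0.005 to 0.02 SD
- 5% vs 1%: 0.02 to 0.09 SD
- 10% vs 2%: 0.05 to 0.18 SD

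**5. Sensitivity to the rule chosen.** If colectomy is instead scored as a bad value (assumed +3 SD), the shift is (pA−pB)(3−d) against the arm with more surgery. For 5% vs 1% this is 0.04 × 1 to 0.04 × 2.5, or 0.04 to 0.10 SD. If imputation from a patient's own earlier scores fully recovered severity, the bias would be about zero. The rule therefore decides the sign of any small difference.

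**6. Scale.** Sample Size and Power gives 119 per group, at least 14 clusters and an ICC up to 0.05. Mean cluster size is 238/14 = 17. With equal clusters the design effect is 1 + 16 × 0.05 = 1.8. The standard error of a difference is √(2 × 1.8/119) = 0.17 SD, if the same ICC holds for SCCAI. A gap of 0.057 SD is about one third of that.

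**The case against.** The strongest reply is that this is a condensed article. Handling of a post-baseline event in two secondary measures usually belongs in the analysis plan, which is not shown, and stopping a colitis index and a stool marker after colectomy is a sensible collection rule. That is fair for the analysis detail, and it is why this part of the point is modest. It does not cover the retention condition, which the article states outright and which contradicts its own text elsewhere. It also leaves a stated imputation commitment with no exception.

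Several stronger readings are tempting, and the documents do not support them.

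- A reader might infer that colectomy is counted nowhere. It is named in the disease-activity objective and reported as a proportion, so an arm with more surgery would show it there. The gap is confined to SCCAI and calprotectin.
- A reader might infer that the arm with more surgery will look better. That needs unequal rates, sicker colectomy patients and a decision to drop them. None of these is given.
- A reader might infer that the regression imputation must be applied to these patients. Its text concerns wholly missing questionnaires.
- A reader might infer that colectomy must be scored as the worst outcome in the main analysis. The article lists colectomy without calling it adverse, and myAID presents surgery as an option. Such scoring is a value judgement, and it reverses the sign.

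It is also true that the interval between receiving the link and viewing myAID is probably short, so few patients may be affected. Patients with acute severe colitis needing inpatient treatment are excluded at entry. The contradiction still needs resolving, because the primary analysis set should not depend on which sentence is followed.

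**Conclusion.** The point holds in two parts. The retention condition is a stated post-randomisation exclusion that differs by arm and conflicts with the follow-up, withdrawal and intention-to-treat statements. It could reach AQoL-8D and the surgery proportion as well as disease activity. Its size cannot be worked out from the documents.

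The cut-off of SCCAI and calprotectin at colectomy could favour the arm with more surgery. The size is about 0.04 to 0.09 SD if one arm has double the assumed rate and exactly the sickest patients are removed, and it varies under milder or more unbalanced assumptions. This is small against a standard error near 0.17 SD and affects secondary outcomes only. The cut-off itself does not touch the primary outcome, because AQoL-8D continues after colectomy.

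**What to change.** 1. Delete the viewing condition from Trial Inclusion Criteria. State that all baseline completers in both arms are retained and analysed as randomised, whether or not myAID was viewed before the colectomy decision. This brings the section into line with Study Flow and Data Collection, Withdrawal and Outcome Data Analysis.
2. State under Missing Data that SCCAI and calprotectin are not imputed after colectomy.
3. Report colectomy by arm beside SCCAI and calprotectin.
4. Add a 6-month analysis that counts colectomy within disease activity, for example a colectomy-free remission proportion, alongside the analysis that excludes colectomy patients. The trial team chooses which leads and records the choice before the data are compared by arm.

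The cost is wording, since colectomy is already collected and validated. The drawback is one additional responder or rank analysis that is less direct than a difference in mean scores.
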